### Recruitment

Recruitment will be conducted through implementing organisations (TDH, WC, DRC) using various outreach strategies including: i) door to door outreach conducted by community outreach teams, ii) referral from existing programmes in the organisation; iii) referral from community-based organisations, and iv) word of mouth resulting in families self-referring and contacting the implementing organisation. Recruitment will be guided by a standard script. At the point of outreach implementing organisations will assess for level of risk using standard procedure, identifying families at medium-high risk usually eligible for focused-psychosocial support programmes, with an adolescent aged 12–17 and consenting to take part. Families meeting these preliminary inclusion criteria will be registered and asked permission for their details to be shared with the research team at the American University of Beirut (AUB).

### Informed consent and assent

Registered participants will be contacted by a research assistant at AUB, and informed consent and assent will be gained over the phone from caregivers and adolescents respectively. The documents will be sent over the phone and read through with oral consent and assent taken. An independent witness (another family member, friend, or neighbour) will be requested to be present during the consent process. The research assistant will sign the form and note the oral consent, and a copy of this will be sent to the family over the phone (via WhatsApp or email). For families who are unable to receive the documents electronically, hard copies will be delivered to their home.

### Screening

After obtaining informed consent and assent, the research assistant will record family demographic data and administer the screening interview over the telephone with each adolescent aged between 12 and 17 years old. Localised guidance [11] to assess participants over the phone and in cramped living spaces will be followed to maximise the privacy of respondents during assessments and to respond to distress or discomfort.

The screening interview with adolescents will consist of the PSC-17 (adolescent report), a brief version of the 35-item PSC measuring symptoms of internalising and externalising difficulties in children and adolescents [12]. The tool has been validated with young adolescents in Lebanon, using semi-structured interviews with psychiatrists as the gold standard [13], and a cut-off of 12 or more is indicative of a need for psychosocial treatment. The family will be eligible to take part if at least one adolescent screens positive on the PSC-17. Where more than one adolescent screens positive, the adolescent scoring the highest will be selected as the index adolescent, and only this adolescent will complete outcome measures at T0 and remaining time points. In the unlikely event of multiple adolescents in the same family scoring the same total score, the oldest will be selected as the index adolescent.

### Randomisation

Randomisation will occur after T0 assessments are completed and will be stratified by site. The unit of randomisation will be families, and they will be randomly allocated to intervention or waitlist with a 1:1 ratio. The randomisation sequence will be computer-generated by a statistician located outside Lebanon, and independent of the study. It will be generated using Research Randomizer (randomizer.org [14]), a computer-based pseudo-random number generator using the “Math.random” method within the JavaScript programming language as the core methods for generating its random numbers. Families are randomised into the intervention group (see details in the “Intervention” section), or a waitlist condition, to receive the programme after post-intervention assessments (T1). They will receive the programme in a group format to assess the feasibility and acceptability of different delivery formats.

To ensure approximately equal randomisation in case smaller numbers of families per organisation are attained than planned, blocking will be used with block sizes unknown to the research team. An unblinded study coordinator will send participant lists (in order of baseline assessment completion date and time) to the independent statistician on a regular basis during the study enrolment period. The independent statistician will then match the randomly generated allocation sequence to the participant list and send this back to the unblinded study coordinator, who will then share participant allocations with implementing teams.

### Outcome measures

We will aim to commence intervention sessions no more than 4 weeks after T0 assessments, and we will aim to conduct T1 assessments within 4 weeks of the 6th session (i.e. approximately 10 weeks after T0); T2 assessments will be scheduled at 12 weeks following T1 (i.e. approximately 19 weeks after T0). Participants will receive 25,000 LL (valued at around $1 using market rates at the time of data collection, due to devaluation of the currency, however providing ample phone data for assessments) per family per assessment to reimburse them for data usage and their time. In case participants do not attend a scheduled assessment, three attempts will be made to contact them in the same week, and once the following week, to schedule a new appointment. This will be done via phone calls, or contacting alternative contacts provided.

The majority of measures have been used in Lebanon previously by the study team in different studies [15, 16]. Two measures that had not been used in Lebanon previously—the Systemic Clinical Outcome and Routine Evaluation (SCORE) Index of Family Functioning [17] and the Difficulties in Emotion Regulation Scale-Short Form (DERS-SF [18])—were translated into simple, non-formal Arabic that can be understood by participants in the region (i.e. Syrians, Lebanese, Palestinians) following recommended procedures for cross-cultural research [19]. Steps involved were as follows: forward translation to Arabic by four team members; independent back translation to English by two people; workshops with English-speaking and bilingual team members to review the translations and ensure they retained the original English meaning; cognitive testing with CAB members to assess comprehensibility, completeness, relevance, and acceptability; review workshops to adjust as needed; and pilot testing with target populations.

All instruments will be delivered via individual telephone interviews by trained research assistants, using the KoBo electronic data collection software on tablets. Assessments will be conducted with the index adolescent, and all caregivers where possible. Prior to taking part in the study, assessors will receive training on the assessments with adolescents and parents, phone delivery, sensitive interviewing, managing distress and risk management, research ethics, gaining informed consent and assent, study procedures and record keeping (using RedCap and KoBo), provision of compensation, risks for bias in collecting quantitative data, adverse events reporting procedures, and data management. Assessors will also role-play the full process from scheduling to assessment and data collection, in Arabic, with multiple opportunities for practice role-plays before taking on families. Ongoing monitoring of assessors’ competency and consistency will be conducted through regular supervision by the PIs.

#### Primary outcome

The primary outcome is psychological distress, as assessed by the Pediatric Symptom Checklist 35 (PSC-35) youth-report [20]. The PSC-35 consists of 35 symptoms (including internalising, externalising, somatic, social, and academic difficulties), rated for their frequency on a 3-point scale ranging from 0 (never) to 2 (often). The total PSC-35 score is obtained by summing scores of individual items and ranges from 0 to 70. In a validation study in Lebanon, the measure showed high internal consistency (*σ* = .80), convergent validity, test-retest reliability, and concurrent validity with psychiatrist clinical assessments [13]. The 17 items of the PSC-17 are identical to those in the PSC-35, and therefore at baseline, screening scores for adolescents on these items will be used, and only the remaining 18 items assessed. We will ensure that there is a maximum of 2 weeks between screening and baseline assessments.

##### Other measures

In order to measure exposure to traumatic events and daily stressors in adolescents as a demographic characteristic and possible moderator of treatment effects, we developed a 36-item inventory to be asked to caregivers. The list was adapted from a traumatic events checklist used in a recent RCT in Lebanon [15], with trauma items being adjusted and daily stressors being added based on formative research for this trial ([name], [name], [name], [name], [name], [name], [name], [name], [name]: Qualitative exploration of family functioning and mental health for at-risk adolescents in Lebanon, in preparation). Each item is scored as ‘yes’ or ‘no’ for occurrence. At T0, we will assess whether these events occurred ever, or in the last month. At T1, we will assess whether daily stressors were present in the last month.

### Intervention

The intervention is a six-session family intervention to be delivered by non-specialist facilitators. Family members will attend weekly two-hour long sessions together, and the programme will be delivered by one facilitator with one family. The first 1.5 h is delivered to the family unit. The final 0.5 h consists of a brief session for the caregivers only. After the 6th session, a booster session of 2 h will be provided after approximately 1 month. The programme was developed by the study team and partners through formative research ([name], [name], [name], [name], [name], [name], [name], [name], [name], [name], [name], [name], [name], [name], [name]: development of the ‘Sawa Aqwa (Stronger Together)’ Family Focused Psychosocial Support Program for at-risk adolescents in Lebanon, in preparation) and covers these main skills: identifying family values, goals, challenges, and strengths; emotional regulation; communication; problem management; managing disagreements; and positive parenting for adolescents. The programme is intended to be delivered face to face in a home visit or in a community centre; however, if safety concerns or restrictions related to COVID-19 prevent this, online modalities will be employed.

Families in the control group will receive the family intervention after T1 assessment. In order to further test the implementation model of the family intervention, the control group will receive a multi-family version of the intervention. Families will be assessed again after the intervention and will also be interviewed to identify implementation and acceptability differences between the versions. Other implementation data, like attendance, fidelity, and dropout, will be collected for both versions of the intervention.

#### Other interventions

Participants will not be prevented from taking part in other interventions during the trial period. There will be no special criteria for discontinuing or modifying allocated interventions. We will ask participants at T1 about other services accessed during the study period.

### Fidelity

To evaluate treatment fidelity, facilitators will complete a session checklist at each session to indicate which components were completed, which family members attended, and whether any rescheduling was needed. A sample of approximately 5% of sessions will be observed by a trained supervisor, who will complete a structured observation form, developed for this intervention, to score which elements of the programme have been carried out by the facilitator and to what quality.

The competency of facilitators will be assessed at the end of training via a 12-item structured rating form, based on the Enhancing Assessment of Common Therapeutic factors [24] rating scale for training and supervision, adapted for working with families. Five of these competency items will also be assessed during each session observation.

### Ethics and trial management

The trial has received local ethical approval from the Institutional Review Board of American University of Beirut (Protocol ID: SBS-2021-0102, 12 October 2021) and will undergo continuing review on an annual basis. On the informed consent form, participants are informed that the study coordinator, or another clinician other than their therapist, is available to them if they are upset by this study, and they are provided with IRB contact details if they wish to raise a concern.

A trial management committee consisting of principal investigators, co-investigators, partner staff, and research coordinator will meet regularly through a series of weekly, fortnightly, and monthly meetings to monitor different aspects of the implementation of study procedures. All adverse events (AEs; e.g. injuries on the way to treatment, increase in distress) and serious adverse events (SAEs; e.g. suicide attempts, serious violence) will be recorded by the research team and reported to a Data Safety Management Board (DSMB), and appropriate response provided. DSMC meetings will be facilitated monthly by a principal investigator, and the board will consist of 3 or more local professionals, external to the study, but with experience in similar research. The PIs are responsible for reporting (S)AEs to the board, and also to relevant ethics committees. The chair or a nominated person from the DSMB will review SAEs within 48 h and the DSMB will review all AEs once a month and where necessary to determine any appropriate action in respect of ongoing trial conduct. If necessary, appropriate action will be taken with respect to individual participants, or conduct of the trial (such as referral to specialised care, installing extra assessment points for monitoring participants, or discontinuation). No interim analyses are planned. The local study coordinator is responsible for ensuring timely follow-up of any (S)AEs and will inform the participants and DSMB if any data indicate that the disadvantages of participation may be significantly greater than expected.

In the case of protocol amendments, the funder will be notified first, followed by requesting amendments from the IRB. The PIs will notify all partners and share updated protocols and standardised operating procedures, and trial registries will be updated. Any deviations from the protocol will be fully documented in a protocol breach log.

### Blinding

Participants and implementation staff will not be blind to participant allocation. The research assistant team completing T1 assessments will remain blind to the intervention allocation of families throughout the trial and will operate independently from the intervention facilitators. All staff have been trained and supervised in the importance of maintaining blinding, and at no time will intentional unblinding of the research assistants be required. Prior to conducting each T1 assessment, instructions will be given by research assistants to all participants about the importance of not revealing their allocation. If the allocation is revealed, research assistants will inform the research coordinator immediately and where possible another research assistant will complete the assessment with that participant and the remaining family members. At the end of each T1 assessment, research assistants will guess which treatment the participant received—if blinding was maintained, this should be no better than chance.

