### Sample size

The sample size calculation was based on a two-group comparison of primary outcome at the post-intervention time point. Assuming a 5% two-tailed significance test, 80% power, it is estimated that data from 270 participants would need to be available at the post-intervention time point in order to detect an effect size of .25. Allowing for 30% attrition, this would correspond to an overall sample size of 351 required at enrolment. A recent individual patient data meta-analysis [10] of psychosocial support interventions for children in low-resource humanitarian settings found an effect size for post-traumatic stress symptoms of 0.33, and functional impairment of 0.29, with no significant effect for depression and anxiety. While our primary outcome is a measure of broad child psychological symptoms, we felt these estimates were most applicable to our study context. Given the novel family systems approach we are employing, we aimed for a conservative minimal detectable effect of 0.25.

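### Assessors guess allocation after hearing the outcome answers, so chance-level guessing is the wrong criterion for an intact blind, and guesses alone do not count disclosures

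*Protocol article*

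**What the plan says.** The Blinding section of the protocol keeps the T1 assessors blind, while participants and implementation staff know the allocation. The check on the blind is this: "At the end of each T1 assessment, research assistants will guess which treatment the participant received", and "if blinding was maintained, this should be no better than chance". The section names no test and no threshold.

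The Outcome measures section makes clear what the assessor knows by then: "All instruments will be delivered via individual telephone interviews by trained research assistants".

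For disclosures, the Blinding section says "If the allocation is revealed, research assistants will inform the research coordinator immediately" and that "where possible another research assistant will complete the assessment with that participant and the remaining family members". The Ethics and trial management section adds a general provision: "Any deviations from the protocol will be fully documented in a protocol breach log". No section says that the guesses will be set beside the number of disclosures.

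**The concern.** The sentence treats chance-level guessing as what an intact blind must produce. That holds only if nothing the assessor hears depends on allocation. The trial's first two hypotheses say the opposite: adolescents and caregivers in the intervention arm are expected to report greater improvement at T1. If so, an assessor with no leaked information can do better than chance from the answers alone. Above-chance accuracy then cannot separate a leak from a treatment effect, and the more effective the programme, the more likely the blind is to look broken.

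The guess statistic also has a limit in the other direction. If a revealed case goes to a second assistant and that assistant's guess is the one counted, the case enters the check as a blind one. A result near 50% would then not show that disclosures were rare.

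What is at stake is how the single-blind claim can be supported when the trial reports. Outcomes are collected by interview from people who know their allocation, so assessor blinding is the stated protection against interviewer bias.

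**Working it through.** **The plan's own figure.** The criterion has no number beyond chance. Since families "they will be randomly allocated to intervention or waitlist with a 1:1 ratio", chance is taken as 50%.

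**Inputs**
- Effect sizes, from Sample size: 0.25 (the design effect) and 0.33 (the larger of the two cited estimates), read as standardised mean differences.
- Number of guesses: 270, the T1 sample in the same section, one guess per index adolescent. Whether 270 is the right sample size is a separate question and does not affect this point.
- Test: the Blinding section specifies none. A two-sided 5% test of accuracy against 50% is assumed, borrowing the level from Sample size ("Assuming a 5% two-tailed significance test, 80% power").
- Also assumed: normal T1 scores with equal spread in both arms, and independent guesses.

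**Step 1: accuracy with no leak.** With 1:1 allocation and one normal outcome differing by d standard deviations, the best possible guess uses a cut-off midway between the arm means. It is right with probability Φ(d/2).
- d = 0.25: Φ(0.125) = 0.550
- d = 0.33: Φ(0.165) = 0.566

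**Step 2: how often the check would flag a failed blind.** For 270 guesses, the exact two-sided 5% binomial test against 50% rejects on the high side at 152 or more correct (152/270 = 56.3%).

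| Situation, no leak in any row | Accuracy | Probability of a false signal |
|---|---|---|
| Guesses unrelated to allocation | 50.0% | 4.4% |
| Half the ideal excess at d = 0.25 | 52.5% | 12% |
| Ideal guess, d = 0.25 | 55.0% | 35% |
| Ideal guess, d = 0.33 | 56.6% | 56% |

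The two ideal-guess rows are ceilings for a guess from the PSC-35 alone. A real assessor does not know the arm distributions and may do worse. Cues from several outcomes together could raise accuracy.

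**Step 3: the effect of reassignment on the guess statistic.** Let u be the share of assessments with a revealed allocation and s the share of those reassigned, with only the second assistant's guess counted. If other guesses are at chance and an informed assessor is always right, accuracy = 0.5 + 0.5 × u × (1 − s). The protocol gives no disclosure rate, so u is an assumption.

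| u | None reassigned | Half reassigned | All reassigned |
|---|---|---|---|
| 10% | 55% (flagged 36%) | 52.5% (12%) | 50% (4.4%) |
| 20% | 60% (flagged 90%) | 55% (36%) | 50% (4.4%) |

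Steps 1 and 3 together show the difficulty. An accuracy of 55% could come from a working programme with no leak, or from 10% disclosure with no reassignment and no treatment effect. An accuracy of 50% could go with 20% disclosure if every revealed case was reassigned.

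**The case against.** Three objections carry weight.

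First, Φ(d/2) describes an ideal classifier. Assessors are not told to guess from scores, and nothing in the protocol depends on the result: no exclusion, no change of analysis, no rule that declares the blind failed. This stands as a limit on size, so 55% is an upper bound and not an expected value, and the 35% and 56% rest on a test the protocol does not name. It does not rescue the sentence, which says what an intact blind should produce and is untrue if the hypotheses hold.

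Second, a reader might infer that reassigning assessors hides breaches from the trial, or that the guess is the only evidence on blinding. The protocol does not support either reading. Every revelation must be reported to the coordinator at once, and there is a log for protocol deviations, although a participant's disclosure is not clearly a deviation. Reassignment happens only where possible, so the remaining cases stay in the check. It is also sound practice: it restores a blind assessor, whose guess is the relevant one for the items that assessor records. The protocol does not say whether items already recorded are kept or asked again, or whose guess is counted. What stands is narrower: the guess statistic, taken alone, does not count disclosures.

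Third, the protocol leaves detailed analyses to a statistical analysis plan that is not shown. The choice of blinding index and any sensitivity analysis belong there, so their absence is not criticised here. The false criterion is stated in the protocol itself and can be judged as it stands.

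**Conclusion.** The point holds in a limited form. Chance-level guessing at the end of T1 is not a valid criterion for an intact blind in a trial whose programme is expected to change the answers the assessor hears. With no leak, accuracy from the PSC-35 alone could reach about 55% at an effect of 0.25 and 57% at 0.33. The corresponding false signals would be up to about 35% and 56%, against 4.4% for pure-chance guessing, and about 12% if assessors achieve 52.5%. These figures assume 270 independent guesses, normal scores and a two-sided 5% test. The direction does not depend on them.

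On reassignment, the conclusion is only that the guess statistic may omit revealed cases and so should not stand alone. Disclosures are reported within the trial and are available to be tabulated. The primary analysis is unaffected. What changes is what the trial can conclude about its blind.

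**What to change.** 1. Delete the statement that guesses should be no better than chance if the blind held.
2. Either record the guess before any outcome items are asked in the family, or keep it at the end and add its reason (told or overheard, versus inferred from the answers) with a don't-know option. An early guess is free of outcome cues but cannot capture a disclosure during the interview, so it depends on item 3.
3. Report the disclosures already notified to the coordinator, and the reassignments that followed, by arm beside the guesses. Treat these as the main evidence on blinding, and state whose guess is counted when an interview is reassigned.

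The cost is one or two extra form items and one descriptive table. Recruitment began in November 2021, T1 falls about 10 weeks after T0, and this version is dated 31 March 2022, so T1 collection had probably started. The new items would then exist only for later interviews, and earlier guesses should be reported separately. Items 1 and 3 need no new data if the coordinator's notifications were kept.
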